**6.2.1.2 Route of Administration**

Panitumumab will be administered as an intravenous infusion.

**6.2.1.3 Preparation of Study Drug**

**NOTE: Panitumumab is a protein and should be handled gently to avoid foaming, which may lead to denaturation of the protein product. This precaution applies not only to panitumumab stored in the vial, but also for diluted panitumumab prepared in the IV bag. It is, therefore, essential to avoid medication delivery methods, particularly pneumatic tube systems that could potentially lead to excessive shaking or vibration that would lead to particulate formation in the protein product.**

The pharmacist, using aseptic techniques, will prepare the panitumumab infusion. The dose of panitumumab will be 6 mg/kg and will be based upon the subject's baseline weight. The dose will not be recalculated unless the weight changes at least  $\pm 10\%$  from the baseline weight. It is recommended that the calculated amount of panitumumab (may be rounded to the nearest tenth milligram [e.g., 456 mg rounded to 460 mg or 312 mg rounded to 310 mg]) is

removed from the vials and added to a total volume of 100 mL of pyrogen-free 0.9% sodium chloride solution. **The maximum concentration of the diluted solution to be infused should not exceed 10 mg/mL.** Doses higher than 1000 mg should be diluted to 150 ml with 0.9% sodium chloride injection. The diluted solution should be mixed by gentle inversion, do not shake. Once diluted, panitumumab should be used  $\leq 6$  hours after dilution if stored at room temperature, or  $\leq 24$  hours after dilution if stored refrigerated at 2° to 8°C (36° to 46°F).

Panitumumab does not contain antimicrobial preservatives or bacteriostatic ingredients.

The bag should be labeled per site pharmacy standard operating procedures and promptly forwarded to the clinic center for infusion.

No incompatibilities have been observed between panitumumab and sodium chloride injection in polyvinyl chloride bags, polyolefin bags, or glass.

Panitumumab 6 mg/kg will be administered IV by an infusion pump through a peripheral line or indwelling catheter using a non-pyrogenic, low protein binding filter with a 0.2- or 0.22-micron pore size in-line filter infusion set-up over 60 minutes by a trained healthcare professional. If a dose of panitumumab is well tolerated (i.e., without any serious infusion-related reactions), then subsequent IV infusions of panitumumab may be administered over 30 - 60 minutes. In the event a subject's actual body weight requires an infusion with a volume greater than 150-mL, panitumumab will be administered over approximately 90 minutes .

Panitumumab should not be administered as an IV push or bolus.

Panitumumab should not be mixed with, or administered as, an infusion simultaneously with other medicinal products. The infusion line should be thoroughly flushed with saline (supplied by the center) before and after administration of panitumumab to avoid mixing with other drug products or IV solutions.

#### 6.2.1.4 Compliance

The investigator or a pharmacist or other appropriate individual, who is designated by the local principal investigator, should maintain records of the inventory at the site, the use for each subject and delivery, storage and destruction. Investigators should maintain records that adequately document that subjects were provided the doses specified in the protocol and reconcile all investigational product(s) received from the sponsor.

The investigator should ensure that the investigational product(s) are used only in accordance with the protocol. All doses given are to be documented in the CRF, including exact dose and date administered.

The investigational product(s) should be stored as specified by the sponsor and in accordance with applicable regulatory requirements.

## 6.2.2 Preparation and Administration of chemotherapy

All drugs used in the study are labeled for treatment of advanced colorectal cancer. Clinical use and administration should follow the respective product/prescribing information. Administration of mFOLFOX6 or 5-FU/ FA chemotherapy will commence on day 1 of each treatment cycle. Chemotherapy will be administered after administration of panitumumab.

### 6.2.2.1 Oxaliplatin

**Mode of action:** DNA cross-linkage

**Administration:** intravenous. For specific formulation, packaging, preparation and administration information, please refer to the instructions provided in the oxaliplatin product labeling. **Oxaliplatin has to be administered before the application of 5-FU. Do not dilute oxaliplatin with NaCl-solution or other chloride containing solutions.**

Aluminium containing equipment should not be used for administration of oxaliplatin as there is a risk of oxaliplatin degradation.

**Common side effects:** nausea, vomiting, diarrhea, leukopenia, thrombocytopenia, anemia, increase of liver enzymes, alopecia, peripheral neurotoxicity.

Please refer to the SmPC for further details.

### 6.2.2.2 5-Fluorouracil

**Mode of action:** anti-metabolite

**Administration:** as continuous intravenous infusion after calculation of the individual 5-FU dose requirement (rounded up to the nearest 10mg)

**Common side effects:** Mucositis, stomatitis, diarrhea, anorexia, alopecia, hematological side effects (mainly leucopenia, more rarely thrombocytopenia). The white blood cell nadir occurs 9-14 days after treatment. Rare side effects are hepatotoxicity, pulmonary toxicity, neurotoxicity, cardiotoxicity and dermatitis. Interaction: Allopurinol should not be co-administered with 5-FU since it may decrease its effect.

**Contra-indication:** Known DPD deficiency. (NOTE: test is highly recommended according to current prescribing information)

### 6.2.2.3 Folinic Acid

**Mode of action:** Folinic acid (FA) stabilizes the complex between FdUMP and thymidilate synthase and thereby increases the inhibitory effect on DNA synthesis.

**Administration:** as intravenous infusion after calculation of the individual FA dose requirement (rounded up to the nearest 10 mg).

**Side effects:** Side effects are gastrointestinal upsets; also allergic reactions are possible. Interactions are conceivable with all drugs that interfere with folinic acid metabolism (e.g., allopurinol, trimethoprim, pyrimethamine). Folinic acid can reduce the therapeutic effects of antiepileptic agents such as phenobarbital, primidon, phenytoin or succinimide and may thus cause an increase in epileptic seizures.

Please refer to the Summary of Product Characteristics for details on description, preparation, administration and precautions for use.

### 6.3 Dose Modifications

Toxicity will be graded according to NCI-CTCAE, version 4.03; the therapy modifications described below are applied according to this severity grading.

Toxicities of severity grade 1 only will not lead to any dose reduction or cycle delay. The same holds for adverse reactions without any potential of serious or life-threatening complications according to the judgment of the physician (e.g., alopecia). Presumably, severe overlapping toxicity between chemotherapy and antibody will not occur (except for diarrhea). Thus, in case of toxicity requiring treatment modification, this alteration should reflect the causal relationship of the respective drug(s). E.g., if the toxicity is unequivocally caused by only one drug, a dosage modification of the other drugs is not required. Likewise, a delay of chemotherapy or the antibody does not lead to the delay of the other modality.

If more than one different type of toxicity occurs concurrently, the most severe grade will determine the modification.

In case of a necessary dose reduction the lower dose level will be applied throughout the rest of the therapy without re-escalation (except for panitumumab, see section 6.3.1). If toxicity requires a treatment delay of more than 3 weeks after the last regularly scheduled dosing date (i.e., 5 weeks after last regular treatment with **all** treatment components), study treatment continuation should be evaluated carefully by the investigator.

In case of acute allergic reactions of grade 3 or 4, the respective agent should be discontinued permanently; in case of grade 1 or 2, it is up to the physician to continue treatment without dose modification and using pre-treatment IV antihistamines and corticosteroids, if this is in the best interest of the patient.

Each dose modification or treatment delay has to be documented in the CRF, including the respective reason.

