### 6.3.1.3 Criteria for withholding a dose of panitumumab

#### Skin- or nail-related toxicities:

- Symptomatic skin- or nail-related toxicity requiring narcotics, systemic steroids, or felt to be intolerable by the subject
- Skin or nail infection requiring IV antibiotic or IV antifungal treatment
- Need for surgical debridement
- Any skin- or nail-related serious adverse event

An algorithm for managing specific panitumumab-related adverse events is shown in Figure 2.

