#### Non-skin- or nail-related toxicities:

- Any grade 3 or 4 toxicity with the following exceptions:
  - Panitumumab will only be withheld for symptomatic hypomagnesemia and/or hypocalcemia that persists despite aggressive magnesium and/or calcium replacement
  - Panitumumab will only be withheld for grade 3 or 4 nausea, diarrhea, or vomiting that persists despite maximum supportive care
  - Panitumumab will only be withheld for grade  $\geq 3$  anemia or grade 4 thrombocytopenia that cannot be managed by transfusion(s) or cytokine therapy

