#### Skin- or nail-related toxicities:

- The adverse event has improved to  $\leq$  grade 2 or returned to baseline or
- The subject has recovered to the point where symptomatic skin- or nail-related toxicity is felt to be tolerable or
- Systemic steroids are no longer required or
- IV antibiotic or IV antifungal treatment is no longer required

Non-skin or nail-related toxicities: Panitumumab administration may be restarted once the adverse event has improved to  $\leq$  Grade 1 or returned to baseline.

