### 6.3.1.5 Dose modification schedule

Subjects should be assessed for toxicity before each dose. Dose modification should be performed according to the schedule described below and outlined in Figure 2.

Subjects who develop a toxicity that does not meet the criteria for withholding a dose of panitumumab (Section 6.3.1.3) should continue to receive panitumumab and their symptoms should be treated.

Panitumumab-related toxicity will be considered resolved if it improves to a degree that allows for re-treatment with panitumumab (Section 6.3.1.4).

For subjects who experience a toxicity that meets the criteria for withholding a dose of panitumumab:

- Subjects receiving either 100% or 80% of the starting dose of panitumumab are allowed to have up to 2 subsequent doses withheld for toxicity. However, a second dose should only be withheld if the toxicity has not resolved by the time that the subsequent cycle of chemotherapy is due.
- Subjects treated at the 100% dose level whose toxicity resolves after 1 dose of panitumumab is withheld should be re-started at the 100% dose level (recommended but not required, reduction to the 80% dose is allowed as an alternative to re-challenge with the 100% dose).
- If toxicity recurs, subjects treated at the 100% dose or 80% dose should be re-started at the 80% dose or 60% dose, respectively, when the toxicity resolves after withholding 1 or 2 doses of panitumumab.
- Subjects treated at the 100% dose level whose toxicity resolves only after 2 subsequent doses of panitumumab are withheld should be re-started at the 80% dose level.
- Subjects treated at the 80% dose level whose toxicity resolves after withholding 1 or 2 doses of panitumumab should be re-started at the 60% dose level.
- Subjects who experience toxicity at the 60% dose level will not be re-treated with panitumumab.

It is recommended that panitumumab doses will be escalated in subjects whose toxicity resolves to the degree that meets the criteria for re-starting a dose of panitumumab (Section 6.3.1.4). Dose escalations are recommended but not required. Dose escalations should occur in the following manner:

- Subjects treated at the 80% dose level whose toxicity does not recur should receive the 100% dose level at the next cycle unless a previous attempt to re-escalate to the 100% dose level was not tolerated (re-initiation of the 80% dose is allowed as an alternative to dose escalation).

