#### 6.4 Preconditions for starting a new treatment cycle

The following requirements have to be met, before a new treatment cycle may be administered:

- No hematological toxicity of grade  $\geq 2$  (i.e., ANC  $> 1,500/\mu\text{L}$ , platelets  $> 75,000/\mu\text{L}$ )
- No stomatitis, nausea, vomiting, diarrhea, hand-foot syndrome or other non-hematological toxicity (except for alopecia) of grade  $\geq 2$
- No ongoing requirement for anti-diarrheic treatment
- Bilirubin  $\leq 1.5 \times \text{UNL}$
- Transaminases  $\leq 2.5 \times \text{UNL}$  in patients without liver metastases or  $\leq 5 \times \text{UNL}$  in the presence of hepatic lesions
- No persisting cardiac toxicity
- No peripheral neurotoxicity of grade 3
- Creatinine clearance  $\geq 30 \text{ mL/min}$
- No treatment delay of more than 3 weeks after regularly scheduled dosing date (i.e. 5 weeks after last regular treatment)

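### Section 6.4, read literally, holds the whole cycle for panitumumab-only toxicity of grade 2 or more that sections 6.3 and 6.3.1 treat without delaying chemotherapy

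*Protocol*

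**What the plan says.** Section 6.4 introduces its list with "The following requirements have to be met, before a new treatment cycle may be administered". One item reads "No stomatitis, nausea, vomiting, diarrhea, hand-foot syndrome or other non-hematological toxicity (except for alopecia) of grade" 2 or more. It does not mention the causative drug, and alopecia is its only exception. A separate item reads "No peripheral neurotoxicity of grade 3". Section 3.1.1 defines a cycle as chemotherapy with or without panitumumab. Section 6.3.2.1, below Table 2, delays treatment by up to 3 weeks when 6.4 is not met.

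Section 6.3 says that a change should follow the drug responsible, and that "Likewise, a delay of chemotherapy or the antibody does not lead to the delay of the other modality". It also lets the physician spare a patient any reduction or cycle delay for reactions with no potential for serious complications, naming alopecia as an example.

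For panitumumab, section 6.3.1.3 withholds a dose for skin or nail toxicity on criteria such as "Symptomatic skin- or nail-related toxicity requiring narcotics, systemic steroids, or felt to be intolerable by the subject"; the others are infection needing IV treatment, debridement and a serious adverse event. For electrolytes it says "Panitumumab will only be withheld for symptomatic hypomagnesemia and/or hypocalcemia that persists despite aggressive magnesium and/or calcium replacement". Below these thresholds, section 6.3.1.5 says that patients "should continue to receive panitumumab and their symptoms should be treated". Section 6.3.1.4 allows restart when skin or nail toxicity is at grade 2 or lower, or when "The subject has recovered to the point where symptomatic skin- or nail-related toxicity is felt to be tolerable". Section 6.3.1.6 gives FOLFOX, and counts the panitumumab dose as missed, when only panitumumab has to be withheld.

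**The concern.** The two sets of rules give opposite instructions for the same patient. A site that follows 6.4 to the letter holds 5-FU/FA for a rash or a low magnesium value that section 6.3.1 does not regard as a reason to withhold even panitumumab.

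In maintenance only arm A receives panitumumab (section 3.1), so holds of this kind would fall mainly on arm A. The intended contrast is panitumumab added to the same 5-FU/FA. A rule that lowers 5-FU/FA delivery in one arm for a toxicity of the added drug works against that contrast. Protocol deviations are also to be counted and listed (section 8.4.1), and the text supports calling either action the deviation: giving the cycle or holding it.

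**Working it through.** The point rests on comparing rules. Three situations, each with toxicity attributed to panitumumab alone:

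| Situation | 6.4 with 3.1.1 and 6.3.2.1 | 6.3 and 6.3.1 |
|---|---|---|
| Tolerable grade 2 rash or nail toxicity | Cycle held | Not a reason to withhold (6.3.1.3); continue and treat (6.3.1.5); no delay of chemotherapy (6.3) |
| Asymptomatic hypomagnesaemia, grade 2 or more | Cycle held | Not a reason to withhold at any grade (6.3.1.3); continue (6.3.1.5) |
| Skin toxicity improved to grade 2 after a withheld dose | Cycle held | Panitumumab may restart (6.3.1.4) |

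The rules differ in all three. Reading 6.4 as a chemotherapy-only rule does not remove the conflict, because it would still hold chemotherapy for a toxicity caused only by panitumumab.

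Which rule is meant to govern can be read from the rest of the text:
- Section 6.3.1.5 permits a second withheld panitumumab dose only if the toxicity is unresolved when the next chemotherapy cycle falls due, so chemotherapy is assumed to be running.
- Section 6.3.1.5 also keeps patients who can no longer tolerate panitumumab on scheduled chemotherapy, and 6.3.1.6 gives FOLFOX when panitumumab is withheld.
- Section 6.4 is called up only from the chemotherapy part (6.3.2.1).
- The separate neurotoxicity item in 6.4 would be redundant if the grade 2 line overrode every specific rule.

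Two related passages carry less weight. Section 6.3.2.2, after a haematological delay, asks for non-haematological recovery to baseline or to grade 1 or lower without regard to cause. Section 6.5.3 treats moderate rash after week 6 with doxycycline and does not mention a hold; that is silence, not a contrary instruction.

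Cost of one delay. Assumptions: a 14-day cycle; maintenance lasting 10 or 7.5 months (the two median PFS values in section 8.2, used only as example durations); 30.44 days per month; a delay of 1 to 3 weeks, the upper value being the limit in 6.3.2.1.
- 10 months: 304.4 / 14 = 21.7 cycles due. One week is 0.5 / 21.7 = 2.3%; three weeks is 1.5 / 21.7 = 6.9%.
- 7.5 months: 228.3 / 14 = 16.3 cycles due. One week is 0.5 / 16.3 = 3.1%; three weeks is 1.5 / 16.3 = 9.2%.

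These are costs per delay. The protocol gives neither the incidence of grade 2 skin or magnesium toxicity in maintenance nor a frequency of delay, so they cannot be scaled to the trial.

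**The case against.** The strongest reply is that no sensible site would follow 6.4 literally. If chemotherapy goes ahead when panitumumab toxicity is bad enough to withhold the antibody, holding it for a milder rash makes no sense. Section 6.3 also gives the physician room to exempt tolerable rash from cycle delay, with alopecia only as an example. This largely stands. A reader might infer from the conflict that sites cannot tell what to do; the documents do not support that, because 6.3.1.5, 6.3.1.6 and the physician clause give workable guidance. What remains is that 6.4 is worded as mandatory, repeats only the alopecia example and does not refer back to 6.3. The physician clause is also not certain to apply, since section 6.5.3 describes infection as a complication of rash and paronychia.

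A second reply is that the consequence is thin, and this also stands in large part. Section 6.5.3 expects acneiform rash to ease after 6 to 8 weeks, which falls within induction. Arm B may carry residual skin toxicity from induction, and in induction and re-induction both arms follow the same rule. Toxicity-driven delay is part of the regimens compared by randomised group. Cycle delay is not a named ground for exclusion from the Per Protocol Population (section 8.3.2), so the direct effect on deviations is on how they are listed.

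**Conclusion.** The contradiction is real and should be corrected. It lies in the wording of 6.4, which conflicts with a principle that the rest of the protocol states and applies. Literal compliance could delay 5-FU/FA mainly in arm A during maintenance, at 2.3% to 9.2% of the cycles due per delay under the assumed durations. The trial-level size is not derivable.

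A reader might go further and infer that 5-FU/FA delivery in arm A was in fact reduced, or that the PFS comparison is biased. The documents support neither. They do not show that any such delay occurred. The stratified log-rank test and the 218-event trigger do not depend on cycle timing, and section 5.1.1 keeps scans at 8-week intervals whatever the cycle delay.

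**What to change.** In 6.4, limit the grade 2 non-haematological line to toxicity related to chemotherapy or of shared or uncertain cause, such as diarrhoea. State that skin, nail or magnesium toxicity attributed to panitumumab alone is handled under 6.3.1.3 to 6.3.1.6 and does not by itself hold chemotherapy, unless there is infection needing IV treatment, a serious adverse event, or the investigator judges chemotherapy unsafe. Refer to this rule in 6.3.2.2, keeping its option of recovery to baseline or to grade 1 or lower. Apply the same rule when classifying deviations at the data review before database lock (section 8.3.2).

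The cost is about three sentences in 6.4 and one in 6.3.2.2, with no change to sample size or analysis. The drawback is timing. Version 9.0 is dated February 2021, and an amendment after it reaches only patients still on treatment. Section 3.4 puts the last patient off treatment at about Q4 2021. The synopsis start of Q2 2014, plus 84 months of accrual, plus about 1 year of treatment gives about Q2 2022. Most cycles will therefore have been given under the present wording. The deviation rule covers all patients.

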#### **1.1.3.2 Clinical experience - safety**

Safety analyses from clinical studies in subjects with mCRC (n = 2588) receiving panitumumab as monotherapy or combination therapy indicated that panitumumab is generally well tolerated.

In these subjects, skin-related toxicities were the most frequently reported adverse events (93% of subjects), with most events being mild to moderate.

Dermatologic toxicities include rash (45%), acneiform dermatitis (39%), pruritus (35%), erythema (30%), and dry skin (22%). Relatively few subjects (2%) permanently discontinued panitumumab due to dermatologic adverse events. Dermatologic toxicities were typically observed after initiation of panitumumab, with a median time to first integument toxicity (of any severity) of 10 days (95% CI: 8, 11). Severe skin toxicities developed in 34% of patients, and <1% of patients developed skin toxicities of NCI-CTCAE grade 4. Rare cases of Stevens-Johnson syndrome and toxic epidermal necrolysis occurred in the postmarketing phase.

Other common treatment-related adverse events (i.e., subject incidence  $\geq 10\%$ ) included gastrointestinal toxicities (diarrhea (50%), nausea (41%), vomiting (27%), constipation (23%) and abdominal pain (23%)), constitutional symptoms (fatigue (37%) and fever (37%)), anorexia (27%) and paronychia (20%). Infusion reactions to panitumumab (defined as any reported allergic reaction, anaphylactic reaction, chills, fever, or dyspnea, occurring within 24 hours of the first dose that were not otherwise designated as either anaphylactic or allergic reaction) were infrequent (4% of subjects; < 1% severe); particularly considering that premedication was not mandated in study protocols.

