### 6.3.1 Dose Modifications for panitumumab

#### 6.3.1.1 Interruption of panitumumab infusion

Subjects who experience any serious infusion reaction during panitumumab administration will have the infusion stopped. Continuation of dosing will be based on the severity and resolution of the event and will be at the discretion of the investigator.

Suspected infusion reactions should be reported as an adverse event. All subjects who experience such an event will be followed for safety.

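### Sections on a grade 3/4 allergic infusion reaction to panitumumab disagree with no stated precedence, and the skin restart list overlaps the withholding list

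*Protocol*

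**What the plan says.** Section 6.3 sets general dose-modification rules for all study drugs. On allergy it states: "In case of acute allergic reactions of grade 3 or 4, the respective agent should be discontinued permanently". For grades 1 and 2 it lets the physician decide whether to continue with antihistamine and corticosteroid cover. Its one reservation for panitumumab ("except for panitumumab, see section 6.3.1") is attached to the ban on re-escalating a reduced dose, not to the allergy sentence.

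Section 6.3.1.1 stops the infusion for any serious infusion reaction to panitumumab and then says: "Continuation of dosing will be based on the severity and resolution of the event and will be at the discretion of the investigator".

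Section 6.3.1.3 lists when to withhold panitumumab. For toxicity outside skin and nails the trigger is "Any grade 3 or 4 toxicity with the following exceptions". The exceptions concern magnesium and calcium, gastrointestinal symptoms, and anemia or thrombocytopenia. Section 6.3.1.4 permits restart at grade 1 or below, or at baseline. Under section 6.3.1.5 a subject at full dose "whose toxicity resolves after 1 dose of panitumumab is withheld should be re-started at the 100% dose level". The same sentence makes this a recommendation and allows 80% instead.

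Section 6.5.1 allows premedication for later panitumumab infusions once a reaction has occurred, whatever its grade.

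For skin and nails, 6.3.1.3 withholds for symptoms that need narcotics or systemic steroids or are intolerable, for "Skin or nail infection requiring IV antibiotic or IV antifungal treatment", for debridement, and for any serious skin or nail event. Section 6.3.1.4 lists four restart items joined by 'or', one of them "Systemic steroids are no longer required or". Section 6.3.1.5 treats a toxicity as resolved once the restart list is met. A footnote to Figure 2 defines recurrence as meeting the withholding list.

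**The concern.** These are operative safety instructions for about 95 centers. If one event falls under several sections with different consequences and no order among them, what happens to the patient depends on which page the site consults. For a severe allergic reaction, the difference is between permanent discontinuation and re-exposure.

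Trial conduct is touched as well. Sections 3.1.1 and 3.2 randomize only patients who qualify for re-induction with all drug components, so the section a site follows after a reaction during induction can decide whether that patient is randomized.

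For skin toxicity, the word 'resolved' does real work in 6.3.1.5. Together with the number of withheld doses it selects the restart level (100%, 80% or 60%), and too many withheld doses end panitumumab for good. If a patient can be resolved and recurring at the same visit, those steps are not defined.

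**Working it through.** No stated design figure depends on this point, so the check is one of consistency.

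**Step 1. One event, each section in turn.** Take a grade 3 acute allergic reaction during a panitumumab infusion that is also serious.

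- 6.3: permanent discontinuation of the causal agent.
- 6.3.1.1: stop the infusion; later dosing at the investigator's discretion.
- 6.3.1.3 to 6.3.1.5: withhold, because allergic and infusion reactions are not among the exceptions. Restart is then permitted at grade 1 or below or at baseline. For a subject at 100% whose event resolves after one withheld dose, 100% is recommended and 80% allowed.
- 6.5.1: premedication may accompany later infusions. Section 6.3 describes premedicated continuation only for grades 1 and 2.

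**Step 2. Precedence.** None is stated. Section 6.3 is specific to the event (allergy) and 6.3.1.1 is specific to the drug (panitumumab), so preferring the more specific rule does not separate them. For oxaliplatin, section 6.3.2.3 has an explicit rule for anaphylactic manifestations. Panitumumab has no counterpart.

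**Step 3. Does the background definition decide the overlap?** Section 1.1.3.2 describes infusion reactions as "defined as any reported allergic reaction, anaphylactic reaction, chills, fever, or dyspnea, occurring within 24 hours of the first dose", but the sentence goes on to exclude reactions otherwise designated as anaphylactic or allergic. It includes and excludes the same events, and it describes past safety data. Seriousness (6.3.1.1) and CTCAE grade (6.3) are also different scales. The boundary is undefined.

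**Step 4. Which actions satisfy which sections?** Permanent stopping is compatible with all of them, since discretion includes stopping and restart in 6.3.1.4 is permissive. Rechallenge is compatible with 6.3.1.1, 6.3.1.3 to 6.3.1.5 and 6.5.1, but not with 6.3. This is a statement of logic, not a view on which rule is right.

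**Step 5. Skin lists.** Code seven yes/no attributes: narcotics, systemic steroids, intolerable, IV anti-infective, debridement, serious event, grade 2 or lower.

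- All combinations: 2^7 = 128. Two have no withholding trigger, leaving 128 − 2 = 126.
- Literal 'or' list: it fails only if grade is above 2 and the toxicity is intolerable and steroids and IV treatment are both needed. The other three attributes are free, so 2^3 = 8 fail and 126 − 8 = 118 meet both lists.
- Crediting only the grade and tolerability items: five attributes are free when both fail, so 126 − 2^5 = 126 − 32 = 94 meet both lists.
- Requiring all four items together: 2^3 − 1 = 7 still meet both, through narcotics, debridement or a serious event.

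These count logical combinations and assume that the attributes vary freely. They are not patient frequencies. A concrete case is a skin infection that the patient now finds tolerable while IV antibiotics are still needed.

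**Step 6. Rough size.** Section 1.1.3.2 gives infusion reactions in 4% of subjects, severe in below 1%, and severe skin toxicity in 34%. With about 400 patients starting induction: 0.04 × 400 = 16; below 0.01 × 400 = fewer than 4; 0.34 × 400 = 136. The first two rest on the definition in Step 3 and on the first dose only. The last counts severe skin toxicity, not patients meeting both lists.

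**The case against.** The strongest reply is that the sections can be read together. Permanent stopping complies with every one of them, the allergy sentence in 6.3 is the only one about grade 3/4 allergy, and 6.3.1.3 is a general toxicity rule. This stands in part. A reader might infer that the protocol obliges some sites to rechallenge, or to restart at full dose. It does not: restart is permissive, and 100% is a recommendation with 80% as an alternative. The reply does not supply precedence between 6.3 and 6.3.1.1, and it does not remove the permission to re-treat given elsewhere.

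A reader might also infer from the background definition that every allergic reaction is an infusion reaction. The exclusion at the end of that sentence rules this out.

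On the skin lists, it is fair to say that 'no longer required' presupposes that steroids were once required, and that 'improved to' does not describe an unchanged grade 2 rash. Section 6.4, which bars a new cycle with non-hematological toxicity of grade 2 or above, also bears on the grade 2 case. Those examples are therefore not relied on. The tolerable infection still on IV antibiotics survives these replies. Pairing each restart item with its own trigger is a possible reading, but it is not written. Under it, debridement and serious events would have only the generic grade-or-baseline item to answer them.

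Figure 2 and the grading manual are not shown. The text says that Figure 2 outlines the same schedule; whether CTCAE grade is tied to IV treatment could not be checked.

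**Conclusion.** The conflict is real but bounded. For a panitumumab reaction that is both a grade 3/4 acute allergic reaction and a serious infusion reaction, sections 6.3, 6.3.1.1, 6.3.1.3 to 6.3.1.5 and 6.5.1 do not agree and none is said to govern. Sites acting in good faith on different sections may stop or re-expose the same patient.

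Few patients are likely to be affected: fewer than 4 of about 400 if the severe infusion-reaction rate is used as a guide. Because that rate's definition excludes designated allergic reactions, it does not size the event at issue. The 136 patients with expected severe skin toxicity show only that the skin lists will be in use.

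The skin point is secondary. It rests on the literal 'or' and on restart items not being tied to the reason for withholding. It lets a patient with a persisting trigger count as resolved, but nothing obliges re-dosing. The sample size, the required number of events and the primary analysis are untouched.

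**What to change.** Reconcile 6.3, 6.3.1.1, 6.3.1.3 to 6.3.1.5 and 6.5.1 so that one named section governs grade 3/4 allergic or infusion reactions to panitumumab, with a cross-reference from the others. State explicitly whether such reactions are inside or outside the general withhold-and-restart scheme, and how grade and seriousness are used to classify them.

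Reconcile the skin and nail lists in 6.3.1.3 and 6.3.1.4 so that no patient can meet a withholding and a restart criterion at the same visit, and bring Figure 2 and its footnotes into line.

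Which rule applies is for the sponsor's clinical team to decide. The cost is wording in a protocol amendment and a letter to sites, with no new data or procedures.
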